#### Intervention Fidelity

The intervention will be delivered to adults as it is designed, seeking to generate the desired changes in the results [26]. For this, it is necessary to develop methodological strategies to ensure the application of the active ingredients (delivery mode, doses, and activities) of the intervention, called fidelity. The fidelity of the intervention contemplates 2 fundamental levels: the theoretical level and the operational level, which are described in Table 1.

**Table 1 table1:** Operationalization of intervention fidelity.

Levels and criteria			Objective		Strategies to ensure fidelity	
**Theoretical**						
	Study design control	Ensure that the intervention is consistent with the theoretical propositions of the Health Promoting Behavior.		The content of the study will be validated by experts to determine consistency between the active ingredients and the proposed theoretical component.		
**Operational**						
	Interventionist training	Ensure that the intervention is delivered in accordance with the protocol.		A course on dengue will be held and nurse training will be provided.		
	Delivery of the intervention	To reduce variability in the application of the intervention.		The intervention will be delivered by a trained nurse and performance will be verified. Development of the intervention protocol manual, with standardized educational material.		
	Treatment exposure	Ensure that all adults receive the intervention on equal terms.		Provide the intervention to all participants as defined in the intervention protocol manual: frequency, dosage, duration, delivery method, and sequence.		
	Treatment reception	Verify the appropriation and use of the active components of the intervention: educational, behavioral, and attitudinal support.		At the end of each session, there will be a space for feedback, review of key points, and commitments.		
	Follow-up of treatment compliance	Verify the implementation of health promoting behavior.		Face-to-face and telephone sessions will be held to provide feedback on the proposed objectives to achieve health-promoting behavior.		

#### Data Collection and Measures

An intervention will be developed in 4 sessions with baseline, end line, and 2-month postintervention measures. The NOC labels chosen to evaluate the effect of the intervention are risk control (1902) and participation in health care decisions (1606).

To characterize the participants in both the intervention and control groups, a form containing variables such as age, sex, education level, marital status, actual occupation, health system affiliation, socioeconomic stratum, and dengue diagnosis will be filled out.

To evaluate the cognitive aspects or mental state of the adult, the mini mental test will be used, which is composed of 30 dichotomous items that evaluate 6 cognitive processes: temporal orientation, spatial orientation, fixation memory, evocation memory, attention and calculation, and language [31,32].

### Outcomes

The outcomes of risk control and participation in health care decisions, which belong to the NOC classification, which is useful for analyzing and measuring the impact and quality of nursing interventions, will be evaluated.

#### Risk Control

Corresponding to code 1902, it consists of 21 indicators on a Likert-type scale with a score from 1 to 5 (1=never demonstrated, 2=rarely demonstrated, 3=sometimes demonstrated, 4=frequently demonstrated, and 5=always demonstrated) and is defined as personal actions to understand, avoid, eliminate, or reduce health threats that are modifiable [33]. It includes items that seek the implementation of behaviors by the adult.

#### Participation in Health Care Decisions

Defined as personal involvement in the selection and evaluation of health care options to achieve a desired outcome, it corresponds to code 1606 and consists of 15 indicators. It uses measurement scale 13, which is defined as the frequency of clarifying by report or behavior and has a score from 1 to 5 (1=never demonstrated, 2=rarely demonstrated, 3=sometimes demonstrated, 4=frequently demonstrated, and 5=always demonstrated) [33]. It contains several indicators that respond to some subconcepts of the theory, such as perceptions of benefits to action, perceptions of barriers to action, and preferences, which are the ones intended to be measured.

### Follow-Up

Participants will be followed up 1 month after the end of the study intervention [34-36]. Individual and face-to-face follow-up is planned to assess the effect of the intervention over time.

### Data Analysis

The information will be tabulated using the EpiData program, and the Stata software will be used for statistical analysis, following the principle of intention-to-treat analysis, which allows the patients to be analyzed as they were originally assigned or randomized [37]. Statistical hypothesis tests will be performed with an α level of 5%. A descriptive analysis of the baseline variables will be made to observe the behavior in each of the groups, using the student 2-tailed *t* test and the Fisher exact test. Categorical variables will be presented with absolute and relative frequencies. Quantitative variables with normal distribution will be presented with mean and SD, and for variables that do not comply with the principle of normal distribution, they will be presented with median and IQR (IQR=Q3–Q1). Normality will be assessed using the Kolmogorov-Smirnov test.

Baseline variables will be compared between the control group and the intervention group. The chi-square test will be used for categorical variables. The student *t* test will be used to compare the means in the 2 groups when the normality assumption is met, and otherwise, the nonparametric Mann-Whitney *U* test will be used.

To control for possible confounding variables, a statistical adjustment will be made through an analysis of covariance with their respective 95% CIs.

The effect of the intervention will be measured through analysis of covariance by means of the delta value or difference of the NOC label score between the 2 comparison groups.

Paired *t* tests will be performed to observe separately how each group fared before and after the intervention and at follow-up.

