Thus, the evidence points to the increase in cases of dengue fever and cognitive and behavioral factors, which will be addressed in light of Nola Pender’s Health Promotion Model (HPM). This model proposes that people interact with the environment, trying to achieve an adequate state of health, schematizing the nexus between personal characteristics and experiences, knowledge, beliefs, and situational aspects linked to the health behaviors or behaviors that are intended to be achieved [22], it raises dimensions and relationships that participate to generate or modify the health-promoting behavior [22], being the positive response that is expected to the actions carried out.

From the HPM perspective, the core concepts and subconcepts are used to achieve health-promoting behavior. Once the individual characteristics and experiences, cognitions, and affects related to the specific behavior are identified, the commitment to an action plan is expected, mediated in the research through the development of the nursing intervention that will generate a behavioral outcome, which is considered the expansion of skills in control behaviors in the prevention and management of dengue (Figure 1).

The objective of this study is to evaluate the effect of a nursing educational intervention to promote dengue control behaviors. We hypothesize that the participants in the intervention group will achieve better dengue control behaviors than participants in the usual care group.

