### Participants, Setting, and Sample

The study participants are rural residents attending health promotion and disease prevention programs in a health care institution located in the municipality of Montería. It is a city in Colombia and capital of the department of Córdoba. It has 490,935 inhabitants and is considered a cattle-raising town.

Participants will be recruited during the opening hours established by the health institution. A sample size of 116 (58 participants for each group) was calculated according to the following parameters: effect size: an expected difference of 0.5 in the score of the nursing outcome labels between both groups [24], a statistical power of 90%, an α type error of 5%, a SD of the outcome scores of 1.0, an average correlation between the first and second evaluations of 0.3, an intervention/control ratio of 1:1, and a loss adjustment of 20%. Stata (version 16.0; StataCorp) software was used for this purpose.

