## Results

It is expected that participants in the nursing education intervention group will have better dengue control behaviors than those in the usual care group (effect size increase of at least 0.5 of the δ score in each of the NOC outcomes). The results are expected to be published in 2025.

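### One hypothesis rests on two equally ranked NOC outcomes with no primary or success rule: error is about 7% to 10% if either suffices, joint power about 81% to 87% if both are required

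*Protocol article*

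**What the plan says.** The Introduction gives one hypothesis: "We hypothesize that the participants in the intervention group will achieve better dengue control behaviors than participants in the usual care group".

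Two labels carry it. The Outcomes section opens with "The outcomes of risk control and participation in health care decisions" and ranks neither above the other. Data Collection and Measures selects both to evaluate the effect, with a baseline measure and two later ones.

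Participants, Setting, and Sample makes one calculation, for "an expected difference of 0.5 in the score of the nursing outcome labels between both groups", with "a statistical power of 90"% and "an α type error of 5"%. It adds an SD of 1.0, a correlation of 0.3 and a 20% loss allowance, and arrives at 58 per arm. It has no step for two outcomes.

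Data Analysis says "Statistical hypothesis tests will be performed with an α level of 5"%. It measures the effect by ANCOVA on the change in label score, without saying which assessment supplies the change. The only tests tied to particular assessments are paired tests within each group.

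The Results section expects "effect size increase of at least 0.5 of the δ score in each of the NOC outcomes".

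**The concern.** Nothing says which result would confirm the hypothesis. The decision is left open between two rules, and each breaks one of the stated operating characteristics:

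- **Either label suffices.** Two chances at 5% give an error rate above 5%.
- **Both labels are required.** Error stays at or below 5%, but a sample size giving 90% for one score does not give 90% for two together.

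If the rule is chosen after the results are known, the reader cannot tell which error rate applied. Interpretation is also at stake. The Risk Control section ties 1902 to behaviors the adult carries out. The section on 1606 says it is meant to capture perceived benefits, perceived barriers and preferences. A positive result on 1606 alone could be reported as confirming a hypothesis about behavior.

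**Working it through.** **Inputs from the protocol article:** difference 0.5, SD 1.0, α 5%, power 90%, correlation r = 0.3, ratio 1:1, loss 20%, 58 per arm, two outcomes, two post-baseline assessments.

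**Assumed:** two-sided tests (two tails are stated only for the baseline *t* test, "using the student 2-tailed"); r = 0.3 between every pair of assessments; correlation ρ between the test statistics of the two labels from 0 to 0.9, since the article gives no figure.

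**1. The plan's own sample size.**
Unadjusted comparison at one time: 2(1.960 + 1.282)² × 1.0² / 0.5² = 84.06 per arm.
ANCOVA on the mean of two post-baseline measures, adjusted for baseline, multiplies this by (1 + r)/2 − r² = 0.65 − 0.09 = 0.56.
84.06 × 0.56 = 47.07, so 48 evaluable per arm; 48 × 1.2 = 57.6, so 58. This matches the stated figure. (Dividing by 0.8 gives 60.)
The other two-sided designs tried give 66 or more per arm. The figure therefore fits one averaged comparison per outcome.

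**2. Either label suffices, one test each.**
Independent: 1 − 0.95² = 9.75%. Correlated values are by simulation from a bivariate normal (table).

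**3. Both labels required, each with 90% power.**
Independent: 0.90² = 81.0%. Otherwise the bivariate normal probability that both statistics pass, Φ₂(1.282, 1.282; ρ).

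| ρ | Error if either suffices | Joint power if both required |
|---|---|---|
| 0 | 9.75% | 81.0% |
| 0.3 | 9.5% | 82.2% |
| 0.5 | 9.1% | 83.2% |
| 0.7 | 8.4% | 84.7% |
| 0.9 | 7.1% | 86.9% |

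**4. Upper case: both labels at both visits, any success counts.**
Independent: 1 − 0.95⁴ = 18.5%. With correlations of 0.3, 0.5 and 0.7 both between labels and between visits: 17.7%, 16.2% and 13.7%.

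**5. Single-visit primary.**
The factor is 1 − r² = 0.91. With 48 evaluable per arm: 0.5 / √(2 × 0.91 / 48) = 2.57; 2.57 − 1.96 = 0.61; power 72.8%.
For 90%: 84.06 × 0.91 = 76.49, so 77 evaluable, or 93 per arm (× 1.2) or 97 (÷ 0.8).

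**6. Cost of holding 90% with two equal outcomes.**
Both required, independent: each needs √0.90 = 94.9% power, so 58 evaluable, or 70 to 73 per arm.
Either suffices, 2.5% each: 56 evaluable, or 68 to 70 per arm; 48 evaluable gives 84.9% per outcome.

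**The case against.** The best defence is that the article condenses a fuller protocol and that multiplicity is commonly handled in an analysis plan, which is not shown. That would excuse silence on technique. It does not excuse the conflict here: the article itself fixes two equal outcomes, an undivided 5% and one power of 90% for one claim.

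Three stronger readings are tempting, and the text does not support them.

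- **An error rate of 18.5%.** A reader might infer four between-group tests from two labels and two post-baseline visits. Data Analysis does not say that the arms are compared at each visit, and the paired tests compare no arms. The sample size fits one averaged comparison per label. Four tests remain possible because the assessment behind the change score is left open. Even then, 18.5% needs independence, which is unlikely for repeated scores on the same adults.
- **A rule that both labels must succeed.** The Results section states an expectation for each label, not a criterion for success. Read as a rule, it would hold error at or below 5%, so inflation and loss of power are alternatives and do not occur together.
- **Power far below 90%.** Under the plan's own assumptions the joint figure is 81% to 87%. Much lower values arise only for a single-visit test, which the article does not specify.

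It is also fair to say that ranking the labels is the investigators' choice. The article links 1606 to the trial's theory and chose both labels to evaluate the effect. So 1902 is offered below as an example.

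**Conclusion.** The concern holds in a limited form. No primary outcome, primary time point or success rule is fixed for a single hypothesis carried by two equal outcomes. The stated 5% becomes about 7% to 10% if either label suffices, or the stated 90% becomes about 81% to 87% if both are required. At 81%, the chance of missing a true effect on both labels is 19%, against a planned 10%. These figures assume two-sided tests, 90% power for each label and a between-outcome correlation of 0 to 0.9. The 18.5% is a ceiling for an analysis the article permits but does not describe. It should not be quoted as the trial's error rate. The point should be settled before any comparison of the arms.

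**What to change.** 1. **Reconcile the follow-up timing.** Data Collection and Measures places the last measure two months after the intervention; the Abstract and Follow-Up place it one month after. No time point can be defined until these agree.
2. **Name one primary label,** for example risk control (1902), analysed by ANCOVA with baseline as covariate on the mean of the two post-baseline measures, at two-sided 5%. This keeps 58 per arm and the planned 90%.
3. **Test 1606 at 5% only if the primary is significant,** and report individual time points as estimates with 95% CIs.

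If the investigators want the labels to count equally, they should state that both are required and restate joint power as about 81% to 87%, or recruit 70 to 73 per arm to hold 90%. A single-visit primary should not be chosen without restating power (about 73% with 48 evaluable per arm).

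The recommended route costs a few sentences and no participants. Its downside is that 1606 cannot be claimed alone if 1902 fails, and the chance of claiming both is still the 81% to 87% above.

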### Ethical Considerations

The trial will be conducted taking into account the ethical guidelines established in the Declaration of Helsinki, the Belmont Report (1979), the Council for International Organizations of Medical Sciences (2002), and Resolution 8430 of 1993 (Ministry of Health, Colombia, 1993). Ethical approval was granted by the Research Ethics Committee of the Faculty of Nursing of the University of Antioquia (#2021-29). Adults willing to participate voluntarily in the study will be selected, applying the principle of fairness, and the information provided by them will be maintained under strict confidentiality. Alphanumeric codes will be used to record the information, and no names or any other personal identification data will be used. The participants in the control group at the end of the research will receive the same educational intervention as the intervention group.

## Results

It is expected that participants in the nursing education intervention group will have better dengue control behaviors than those in the usual care group (effect size increase of at least 0.5 of the δ score in each of the NOC outcomes). The results are expected to be published in 2025.

## Discussion

### Principal Result

Dengue is linked to household sanitation. The existence of breeding sites is due to specific human behaviors that favor them, whether individual, community, or institutional [15]. Insufficient knowledge about the disease is one of the factors that precipitates the application of inadequate measures [38,39].

Research indicates that risk factors are fostered by the community, largely caused by artificial reservoirs or unprotected tanks in homes [40,41]; it also indicates that the lack of information hinders the identification of symptoms [38] and the poor application of effective measures.

In the study scenario, there is evidence of inadequate knowledge and practices regarding dengue [20], aspects that this study seeks to improve in order to generate favorable changes in the behavior of the population and, therefore, of the disease.

The results of the research may serve as a basis for the identification of lines of action that should be strengthened in the prevention and control of dengue, including the induction and reinduction of the human talent necessary for health care.

Likewise, the research is a window for theoretical-practical integration in health promotion scenarios, and at the same time, it is configured as an opportunity for the visibility of care and its standardization in the rural population. It is hoped that the results will serve to strengthen the role of nursing as an active member of health risk management.

### Limitations

Length of follow-up, cointerventions, and attrition during the study are anticipated limitations. To reduce these limitations, the selection of participants will be controlled by random assignment to the intervention, specific eligibility criteria for entry into the study, and intention-to-treat analysis. Both the intervention and outcome assessors will receive appropriate training. Masking and adjustments to the statistical analysis will be performed as needed. Health care professionals will be sensitized to avoid cointervention in the study. The principal investigator will be the study supervisor and will not be involved in intervention delivery or outcome assessment.

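### Intention-to-treat as defined here does not deal with attrition, and ANCOVA on a follow-up delta, run as written, leaves out end-line scores that are collected

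*Protocol article*

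**What the plan says.** Limitations (Discussion) gives three anticipated limitations, one of which is attrition. The measures offered in reply are random assignment, "specific eligibility criteria for entry into the study, and intention-to-treat analysis". The section then adds training, masking, unspecified analysis adjustments where needed, and sensitising staff against cointervention.

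Data Analysis commits to "following the principle of intention-to-treat analysis, which allows the patients to be analyzed as they were originally assigned or randomized". The effect is to be "measured through analysis of covariance by means of the delta value or difference of the NOC label score" between the groups. The section does not say which visit the delta refers to, whether baseline is a covariate, or how a participant without a later score enters the model.

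Data Collection and Measures schedules a baseline score and two later ones: at end line and at a postintervention follow-up. Participants, Setting, and Sample includes in the calculation "and a loss adjustment of 20" per cent.

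**The concern.** Analysing people in the arm to which they were randomised settles where they are counted. It does not create an outcome for someone who has none. Random assignment and eligibility criteria act before anyone is lost, so they do not correct attrition either. The article therefore presents as protection something that its own definition cannot give.

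The named model makes this matter. A delta needs a baseline and a later score. If the later score is the follow-up one, a participant seen at end line but not at follow-up contributes nothing, although an informative score has been recorded.

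The intervention arm attends four weekly face-to-face sessions, and the article describes no matching visits for usual care. Loss that differs by arm is thus plausible, though the document does not state it. If the intervention participants who leave are those who responded less, those who remain overstate the effect.

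**Working it through.** **1. The stated sample size.** The article says "A sample size of 116 (58 participants for each group) was calculated according to the following parameters": difference 0.5, SD 1.0, correlation 0.3, 90% power, 5% alpha (taken as two-sided), ratio 1:1, 20% loss. Take ANCOVA with one baseline and two follow-up measures, all correlated 0.3:

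- variance factor = (1 + 0.3)/2 − 0.3² = 0.65 − 0.09 = 0.56
- n per arm = 2 × (1.960 + 1.282)² × 0.56 / 0.5² = 47.07, so 48
- 48 × 1.20 = 57.6, so 58 per arm and 116 in total

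This is an exact match. Dividing by 0.80 instead gives 60 per arm, 120 in total. ANCOVA on a single follow-up gives 186 or 194, and a change score on a single follow-up 284 or 296, depending on how loss is added. The 116 is therefore consistent with both post-baseline scores being used, though the article does not say so.

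**2. What the loss allowance means.** 116 × 0.20 = 23.2, so about 23 people without a follow-up delta if loss reaches the allowance. 58 × 0.80 = 46.4, so about 46 per arm remain. Power at 46 per arm under the variant in step 1 is 89.3%. The issue is bias, not power.

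**3. Possible bias.** The documents do not allow this to be computed, so the inputs are partly assumed.

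- From the article: true effect 0.5, SD 1.0, baseline correlation 0.3, 20% loss.
- Assumed: everyone is measured at end line and loss follows. Loss is random in controls. In the intervention arm it is logistic in the end-line score (low scorers leave more often, slopes 0.7 and 1.5 per point), calibrated to 20%. The end-line/follow-up correlation is 0.3, 0.6 or 0.8.

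Each range runs from the weaker to the stronger slope:

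| End-line/follow-up correlation | ANCOVA adjusted for baseline | Unadjusted delta | Analysis also using end line |
|---|---|---|---|
| 0.3 | 0.53 to 0.54 | 0.50 | 0.50 |
| 0.6 | 0.57 to 0.61 | 0.54 to 0.56 | 0.50 |
| 0.8 | 0.60 to 0.66 | 0.56 to 0.61 | 0.50 |

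Repeat runs differ by about 0.01. The last column is the regression of follow-up on baseline and end line within each arm, applied to everyone; this is the mixed model's equivalent when loss occurs only after end line. ANCOVA on the delta with baseline as a covariate gives the same group estimate as ANCOVA on the final score, so the second column applies if baseline is a covariate and the third if it is not.

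**4. Loss before end line.** If the same loss happens before the end-line score is recorded, the mixed model has no post-baseline data on those lost. At correlation 0.6 it then keeps the bias of the ANCOVA (0.56 to 0.61).

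**The case against.** A reader might infer that the main result will be a completers' analysis that drops everyone without a final score. The document does not support that. It does not exclude imputing scores before the ANCOVA, and handling of missing data is often left to a full protocol or analysis plan, which is not shown. No time point is given for the delta, so an end-line delta could keep late dropouts. The 20% is a planning allowance, not a forecast. Limitations also answers three problems with one bundle of measures and does not pair intention-to-treat with attrition alone. All of this stands, and it limits the point to the analysis run as written with no further step.

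The size is also open to challenge. One-sided informative loss, the slopes and the correlations of 0.6 and 0.8 are not in the document. Its only correlation is 0.3, stated for the first and second evaluations. If 0.3 also holds between end line and follow-up, as in the calculation that reproduces 116, the unadjusted delta is unbiased and ANCOVA is off by only 0.03 to 0.04. Even at 0.6 the ANCOVA bias of 0.07 to 0.11 is below one standard error: √(2 × 0.91/46) = 0.20. Because simulated loss depends only on a recorded score, the analysis using end line returns 0.50 by construction.

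Lastly, session burden acts before end line, and the mixed model does not recover people lost then. That stands as a limit of the remedy. It does not make the statement about intention-to-treat correct.

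**Conclusion.** The point holds in a limited form. As defined in Data Analysis, intention-to-treat fixes group assignment and does nothing for participants without a later score, so it should not be listed among the measures against attrition. An ANCOVA on a follow-up delta, run with no other step, would ignore end-line scores already collected.

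Whether this biases the result depends on loss that is related to the end-line score and differs by arm. Under the assumed mechanism, with 20% loss and a true effect of 0.5, the baseline-adjusted estimate is too high by about 0.03 at the lower end (correlation 0.3) and 0.16 at the upper end (correlation 0.8), that is, 6% to about one third of the effect. For the unadjusted delta the range is zero to 0.11. Random loss, or loss alike in both arms, would not produce this differential bias. The correction is worth making because it is cheap and uses data already scheduled.

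**What to change.** 1. In Data Analysis, replace the ANCOVA on the delta with a linear mixed model of the end-line and follow-up scores: group, visit, group × visit, baseline score × visit, and unstructured covariance within participant. Include every randomised participant with at least one post-baseline score.
2. Name the contrast that measures the effect. The 116 matches the average over the two visits. For the follow-up visit alone, ANCOVA at 46 per arm has about 71% power for a difference of 0.5.
3. In Limitations, remove intention-to-treat as an answer to attrition and say that it governs assignment only.
4. Add a sensitivity analysis that includes all 116, with those lost before end line, because the model assumes missing at random and cannot recover them. One option is multiple imputation with the imputed intervention scores shifted over a stated range. To show the scale: if those observed show 0.5 and the effect in the lost 20% is 0.25, 0 or −0.5, the effect in all randomised is 0.8 × 0.5 + 0.2 × that value = 0.45, 0.40 or 0.30.

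The cost is a few lines of text, one Stata mixed-model command and one sensitivity analysis. No new data, visits or participants are needed.
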